### Secondary outcome measures

The proficiency of clinicians in assessing and managing children presenting with respiratory illness will be assessed via medical record audit of clinicians recording: (i) cough presence, (ii) cough quality, (iii) cough duration, and (iv) correct management if suspected PBB.

The medical record audit period will occur in the same two, six-month periods pre-and post-intervention

iii)
**Economic evaluation**
Economic evaluation will be conducted from a society and health system perspective. Cost data for the economic evaluation will be sourced directly from medical clinic records and will include all costs associated with the intervention, including the training workshops and health information campaigns. We will also collect health care utilisation data 6-months pre-and post-intervention from patient electronic health records. Outcomes for our economic evaluation will be based on the proportion of clinicians adhering to guideline recommendations, as well as patient-relevant outcomes, i.e., the proportion of patients at risk of developing bronchiectasis. Given the non-randomised study design, incremental outcomes for the economic evaluation will be calculated as the difference between proportions before and after the intervention, which adjust for seasonality. The trial-based cost-effectiveness analysis will calculate (a) the cost per additional clinician (compared to pre-intervention) providing optimal management of chronic wet cough and (b) the cost per additional patient (compared to pre-intervention) avoiding bronchiectasis.In addition to the above analyses, we will conduct a modelled cost-effectiveness analysis to estimate the cost per case of bronchiectasis prevented, based upon the assumption that at least 40% of children with chronic wet cough have PBB and will develop bronchiectasis if undetected and/or sub-optimally managed. The results will be plotted on a cost-effectiveness plane. Bootstrapping and Monte Carlo simulation will be used to estimate a confidence interval around costs and health outcomes. A one-way sensitivity analysis will be conducted around the key variables. A probabilistic sensitivity analysis will be conducted to estimate the joint uncertainty in all parameters. A cost-effectiveness acceptability curve will be plotted. Such a curve provides information about the probability that an intervention is cost-effective, given a decision maker’s willingness to pay for each additional child avoiding bronchiectasis.iv)
**Implementation outcomes**

Implementation outcomes will be used to measure how successful the program was implemented [24].

Fidelity to core components of the program will be assessed as per Table 1 outcomes.Acceptability for both HCPs and parents (i.e., the perception among implementation stakeholders that the program is agreeable, and satisfactory27) and feasibility (i.e., the practicability and suitability of the program for everyday use 27) will be assessed through semi-structured interviews. (See Additional file, Appendix 1 and 2).Appropriateness: (“the perceived fit of the program for the given practice setting”.27) Assessment will be through two tools. Firstly, a 22-item Workshop Evaluation (WEVAL) and secondly a 14-item Workshop Assessment Follow-Up (WAFU). The WEVAL evaluates perceptions of the program directly after implementation (
http://ibr.tcu.edu/wp-content/uploads/2013/06/weval.pdf
) and the WAFU evaluates changes 6-months later. (
http://ibr.tcu.edu/wp-content/uploads/2013/06/wafu.pdf
). (Note, the evaluations have been amended with approval from the authors for local use, e.g., removal of social security number)Assessment of implementation cost is described under the economic analysis section below.Penetration and adoption (i.e., the degree of update and spread of implementation27) will be assessed as 1) the number of HCPs undertaking training out of the total number of HCPs employed, and 2) audit of medical records per secondary outcome measure description.Sustainability (i.e., “the durability of the implementation and the degree it can be maintained”27) will be assessed by questionnaires, interviews and/or focus groups with HCPs and parents in the final months of the study.

The evaluation of implementation outcomes will regard the diversity within First Nations contexts [25]. Assessment of acceptability (b, above) and appropriateness (c above), will include identification of co-design, leadership, governance, and involvement in all processes of implementation by First Nations.

### Participant timeline

The timeline for the study and participants is outlined in Table 2.

**Table 2 Tab2:**
[figure not shown]
Conceptual timeline of study for ALL sites^a^

*Legend*: *Q* Quarter

^a^The above timeline applies to individual study sites/clusters. The timing of Q1 at each site or cluster will vary

### Sample size

The 8-item version of the PC-QOL will be the primary outcome measure. Unpublished data from our previous research suggests a conservative standard deviation of 1.3, a nil-intervention mean score of ~ 2.7 and a post-intervention mean score of ~ 4.3 The study’s power was examine using two approaches, a ‘per site’ intervention perspective (using a two-sided T-Test methodology) and a ‘whole of study’ intervention perspective (using clustered analysis to control for the within-site variation).

The ‘per site’ perspective suggests that with a minimum of 12 participants (that have chronic wet cough in each period) there will be > 80% power to detect a difference of 1.6 between the nil-intervention and post-intervention periods, alpha 0.05. The ‘whole of study’ perspective suggests that with a minimum of 5 participants per cluster (4) per period there will be > 95% power to detect a difference of 1.6 between the nil-intervention and post-intervention periods (assuming COV 0.65, ICC 0.01, alpha 0.05); with a minimum of 10 participants per cluster (4) per period there will be > 80% power to detect a smaller difference of 0.9 between periods (assuming COV 0.65, ICC 0.01, alpha 0.05). The presented calculations, carried out using PASS [26], are not adjusted for multiple comparisons as they were simply carried out to provide guidance during study design given, ultimately, the achievable final sample size is contingent on both cohort sizes and CWC incidence during the study periods.

### Health-seeking

Our recent study at a single AMS showed that only 1.6% of the 634 children who attended clinic over a 6-month period pre-intervention were seeking help for chronic wet cough. Assuming that health-seeking rates will be similar across study sites, this study aims to at least double this rate at each study site, for which we will have at least 80% power to detect such an improvement at the 0.05 level of significance.

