**Health-seeking**
This outcome is the number of parents seeking help at the local clinic for their child's chronic wet cough during a six-month period pre-and post-intervention. We will use clinic record audit to compare patients in a 6-month period the year before implementing the intervention, up to patients during 6-months directly after the intervention is implemented. Hypothesis: significantly more parents will seek medical attention for children with ongoing wet cough in the year after the intervention than in the preceding year. Numbers will be normalised to clinic activity over each corresponding 6-month period. To minimise the effect of seasonal factors influencing results, the same six calendar months will be audited pre-and post-intervention and will take into account the seasonal respiratory viral infections.ii)

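### The claim of at least 80% power to detect a doubling of health-seeking at each site is not supported by its own inputs: at the one clinic size given, power is about 46% two-sided or 59% one-sided

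*Protocol article*

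**What the plan says.** The Health-seeking paragraph that follows the Sample size section of the Protocol article rests on a single earlier observation: "only 1.6% of the 634 children who attended clinic over a 6-month period pre-intervention were seeking help for chronic wet cough". It carries the rate, but not the clinic size, over to the trial ("Assuming that health-seeking rates will be similar across study sites"). It then sets the target and the power together: "this study aims to at least double this rate at each study site, for which we will have at least 80% power to detect" such a change "at the 0.05 level of significance". It names no test, no sidedness and no denominator for any trial site.

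The comparison itself is fixed under Outcomes, Health-seeking: "We will use clinic record audit to compare patients in a 6-month period the year before implementing the intervention" with patients seen in the six months directly after it, over the same calendar months, with counts normalised to clinic activity. The hypothesis there is directional and is worded in terms of a significant increase. Under Statistical methods, chi-squared tests are named as an example for simple comparisons of secondary outcomes.

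**The concern.** A comparison of two audited periods has sampling error on both sides. At 1.6% of 634 the baseline is about 10 children and a doubling is about 20. A difference between counts that small is hard to separate from chance, so 80% power at a single site of that size looked too high.

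Improving carer health-seeking is the first specific objective, and the Discussion foresees comparing the program's efficacy between sites. If per-site power is well below what is stated, readers will expect more of a site-level test than it can deliver, and an inconclusive result at one site will be harder to interpret correctly.

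**Working it through.** **Inputs.** p1 = 0.016 and n = 634 (Health-seeking paragraph after Sample size). p2 = 0.032, the smallest effect that meets the target. Alpha = 0.05 (same paragraph). Two observed periods (Outcomes, Health-seeking).

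**Assumptions.** 634 children in each period at a site, since no other clinic size is given. Equal period sizes. Sidedness is not stated, so both cases are shown.

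**Step 1: can the stated figure be reproduced?** Only by treating 1.6% as a known constant and testing the post-intervention rate against it:

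- Null SE = sqrt(0.016 × 0.984 / 634) = 0.00498
- Alternative SE = sqrt(0.032 × 0.968 / 634) = 0.00699
- Power = Φ[(0.016 − 1.96 × 0.00498) / 0.00699] = Φ(0.89) = 81% two-sided

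An exact one-sided binomial test against a fixed 1.6% gives 80%. Neither is the planned comparison, because the pre-intervention period is itself a sample.

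**Step 2: the planned two-sample comparison.**

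- SE = sqrt[(0.016 × 0.984 + 0.032 × 0.968) / 634] = sqrt(0.04672 / 634) = 0.00858
- 0.016 / 0.00858 = 1.86
- Two-sided power = Φ(1.86 − 1.96) = 46%
- One-sided power = Φ(1.86 − 1.645) = 59%

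**Step 3: does the choice of test matter?** Two-sided power at 634 per period:

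| Method | Power |
|---|---|
| Pooled z | 46.1% |
| Unpooled z | 46.2% |
| Arcsine | 47.1% |
| Poisson log rate ratio | 43.7% |
| Chi-squared, exact enumeration | 46.6% |
| Chi-squared, continuity-corrected | 38.8% |
| Fisher exact | 40.1% |

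One-sided, the pooled z gives 58.6% and Fisher 52.0%. Letting 1.6% stand for anything from 1.55% to 1.65% moves the two-sided figure only from 44.9% to 47.2%. Making the post-intervention period five times larger raises it only to 60.8%.

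**Step 4: what would give 80%?** With mean rate 0.024:

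- n = [1.96 × sqrt(2 × 0.024 × 0.976) + 0.842 × sqrt(0.04672)]² / 0.016² ≈ 1,436 per period
- With 1.645 in place of 1.96, n ≈ 1,131 per period

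1,436 / 634 is about 2.3 times the clinic size given. Holding n at 634, a 2.6-fold rise has 77.9% two-sided power and a 2.7-fold rise has 81.6%.

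**Step 5: other clinic sizes (assumed).** Two-sided power for a doubling is 31% at 400 children per period, 65% at 1,000 and 82% at 1,500.

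**The case against.** **Clinic size.** The article extends the rate to all sites, not the figure of 634. The sites differ widely, several are not described by size, and the Northern Territory sites are still to be advised. A site with about 1,436 children per period would meet the claim. This stands: a reader might infer that the 80% is false at every site, and the article does not give the denominators to show that. But the claim covers each site, so it needs every site to be that large, and nothing stated supports this.

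**Sidedness.** The hypothesis is directional, so a one-sided test is arguable. Power is then 59%, still short of 80%. It does rule out a flat statement that a doubling would be missed more often than found, which holds only for a two-sided test at this size.

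**A study-level reading.** One could attach the power clause to the study as a whole. The sentence ties the improvement to each study site, and the PC-QoL calculation shows that the authors distinguish a per-site from a whole-of-study view, so this reading is strained. A reader might still infer that pooling settles the matter, since four sites of 634 give about 96%. That figure assumes four equal sites and ignores clustering and site-by-period variation. As an illustration, let the log rate ratio vary between sites with an assumed SD of 0.3. Its SE over four sites is sqrt[(1/10.14 + 1/20.29 + 0.09) / 4] = 0.244, and ln 2 / 0.244 = 2.84. Power is about 81% with a normal reference and about 49% with a t reference on 3 degrees of freedom.

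**Weight.** PC-QoL is the primary outcome, and Statistical methods puts effect estimates with confidence intervals ahead of significance. So the article does not support the inference that a non-significant site would be declared a failure. The remark in Sample size that its calculations were for guidance is attached to the PC-QoL figures; the health-seeking claim carries no such qualification.

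**Conclusion.** The point holds in a limited form. The stated per-site power does not follow from the inputs printed beside it. At the only clinic size given, power to detect a doubling is about 46% two-sided or 59% one-sided, and no two-sample calculation tried at 634 per period came near 80%. The shortfall is about 34 percentage points two-sided and 21 one-sided.

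This rests on 634 children in each period at a site, on equal periods, and on the two periods being treated as independent samples.

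The agreement with a one-sample calculation suggests how the figure may have arisen, but the article names no method, so that remains a guess. The error lies in a stated power for a named objective that is not the primary outcome; it does not undermine the primary analysis.

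**What to change.** Replace the per-site claim of 80% with the power of a two-sample comparison of the two audited periods, calculated at each site's expected number of children per period, and state the test and the sidedness. For a site of 634 per period the entry would read about 46% two-sided (59% if a one-sided test is chosen and justified), with about 1,436 per period (1,131 one-sided) needed for 80%. Report site-specific rates as estimates with 95% confidence intervals.

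If a whole-of-study power is to be claimed instead, calculate it for the actual number and sizes of sites, with an allowance for clustering and site-by-period variation. Do not insert the unclustered 96%. Moving the powered hypothesis from each site to the pooled sites would be a design decision and should be recorded as one.

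The cost is a short calculation and a reworded sentence with a less favourable figure. The audit takes whoever attends, so recruitment does not change.

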#### Pragmatic data collection

Ultimately, the power of the study will depend on the ability to recruit participants from the limited pool of diagnosed patients within the study population. We estimate that within each of the two stages, somewhere between 12–20 eligible children will be recruited (based on data from the first and completed study site [9]). Thus, we aim to have data for 12 participants per combined regional sites (study cluster) per stage.

### Recruitment

#### Recruitment for QOL survey in nil-intervention and post-intervention groups

Participants will be recruited following a medical record audit identifying children who presented for chronic wet cough or who had multiple presentations for cough and chronic wet cough. This will be subsequently confirmed through parental history from interviews conducted by two researchers (including at least one specialist clinician). Children will be excluded if they are non-First Nations, if they do not have a chronic wet cough (i.e., a daily wet cough ≥ four-weeks) or if the family is unable or unwilling to give informed consent (Fig. 2).

**Fig. 2 Fig2:**
[figure not shown]
Recruitment process for cough related quality of life surveys. Legend: PCH-QoL = parent proxy cough related quality of life

#### Recruitment of interviews with parents/carers

Posters advertising the study will be placed in clinic waiting rooms and strategic community settings. Parents who respond to the poster by contacting the study team will potentially be recruited. Parents of children who have presented to the clinic with their child with repeated respiratory infections or for chronic wet cough who are identified for the PC-QoL tool will also be invited to participate in an interview at the time of their appointment for the PC-QoL tool. Snowball sampling will be employed to recruit more widely to ensure views are gathered from other families who do not necessarily have children with chronic wet cough to ascertain knowledge of other community members in general.

#### Recruitment of HCPs

Clinic staff will be identified via the management of the clinic. Hospital staff will be identified via clinical and management leaders. Snowball sampling will be employed to recruit more widely to ensure views are gathered from all key stakeholders in the outer setting.

#### Plans for assessment and collection of outcomes

Health-seeking data will be collected through an audit of medical records by a clinician-researcher and entered into REDCap [17, 18]. Clinician management of chronic wet cough will be collected from medical records, with data entered into REDCap. The PC-QoL questionnaire [23] will be administered to eligible participants. The PC-QoL questionnaire [23] has eight questions rated on a Likert scale, and is administered using REDCap. Qualitative data will be collected via the interviews and focus groups, transcribed, and then analysed, as described in Sect. 11b, page 14.

Site coordinators will regularly monitor data collection and source documents. The study database will be monitored for missing data or errors in data entry.

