4. Educational resources for HCPs	1. Health information flip chart/leaflets 2. Animated film version of flip chart 3. Flow chart on wall in clinic as reminder	• Champion at each site ensures availability and accessibility of documents	• Educational resources adapted for each site (including language translation) • Available on internet/intranet	• Record whom information resources are given to
5. Practice changes	• Ensure that clinical practice guidelines easily accessible • Call-back option (ability to schedule follow-up of patient by same clinician) • Electronic decision support, if feasible, e.g., prompts to ask about cough quality and duration. Ensuring clinical practice guidelines (a precondition) easily accessible • Provision for nurses to allow initiation of medication treatment context-specific to chronic wet cough • Facilitate medication dispensing, e.g., home visits by health staff, patients attending clinic to receive their medication can bypass triage for medication administration	• Clinical manager to implement practice changes	• Booking system for recall of patients operational • Flow charts placed in clinic rooms • Flexibility in medication dispensing system	• Record if booking option operational • Record flow chart placements • Record of clinic-assisted medication administration • Record of nurses who complete training and can initiate medication treatment
6. Local champions	Facilitated uptake of new processes by local HCPs	• Identified by research team and/or clinical lead at each site	• Champion is trained and at each site	• Presence of champion and input from champion at each site

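### Health-seeking is counted from clinic notes whose recording of cough the program also aims to improve, so part of any rise may reflect better recording rather than more parents seeking help

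*Protocol article*

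**What the plan says.** Under Outcomes, item (i) Health-seeking, the protocol article states: "This outcome is the number of parents seeking help at the local clinic". The source is given there ("We will use clinic record audit to compare patients in a 6-month period the year before implementing the intervention") and again under Plans for assessment and collection of outcomes ("Health-seeking data will be collected through an audit of medical records by a clinician-researcher"). Two safeguards are stated: the same calendar months are audited before and after, and "Numbers will be normalised to clinic activity over each corresponding 6-month period".

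The program acts on what those notes contain. Under Medical clinics, one of the messages to clinicians is to take a history of cough quality and duration. Table 1, component 5, adds, if feasible, electronic "prompts to ask about cough quality and duration". Table 1, component 3, adds monthly feedback from audits of the records.

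Under Secondary outcome measures, the same kind of recording is an outcome in its own right: "medical record audit of clinicians recording: (i) cough presence, (ii) cough quality, (iii) cough duration". It is audited in the same two six-month periods.

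The section on recruitment for the QOL survey describes chronic wet cough as "a daily wet cough ≥ four-weeks", that is, by quality and duration together.

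**The concern.** An auditor can recognise a chronic wet cough presentation more readily when the note says that the cough was wet and how long it had lasted. The program sets out to make notes say this more often. If it succeeds with clinicians (objective 2), the audited count for carers (objective 1) can rise even where carers behave as before.

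At each site the community campaign and the clinician training run in the same three-month period (Table 1, components 3 and 7). A before-after contrast therefore cannot tell the two routes apart.

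Neither stated safeguard deals with this. Matching calendar months handles season. Normalising to clinic activity handles volume, and the program may itself change that volume through recall visits ("Call-back option (ability to schedule follow-up of patient by same clinician") and clinic-assisted medication visits. Confirmation by parental history is described only for recruitment to the PC-QoL survey, after the audit has already found the child. At stake is whether a rise may be reported as more parents seeking help.

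**Working it through.** **Plan's own figures (Sample size, Health-seeking).** The baseline is 1.6% of 634 children in six months: 0.016 × 634 ≈ 10 children. The aim is at least a doubling at each site, to 3.2%: 0.032 × 634 ≈ 20 children. At least 80% power is stated, without a number of children per site. Taking 634 per period as an assumption, a two-sided comparison of 1.6% with 3.2% at 0.05 (pooled variance) has 46% power, and 80% needs 1,436 per period. That gap is a separate matter, and nothing below depends on it.

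**Model.** Let T be the true proportion of attending children brought for chronic wet cough, and s the probability that the notes let the auditor identify such a child. Subscripts 0 and 1 denote before and after.

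- Recorded rate: R = T × s
- Ratio observed: R1/R0 = (T1/T0) × (s1/s0)
- With behaviour unchanged (T1 = T0): R1/R0 = s1/s0

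**Numbers.** The document gives neither s0 nor s1, so every value below is an assumption. R0 is fixed at 1.6% and behaviour is unchanged.

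| s0 | s1 | s1/s0 | Recorded rate after |
|---|---|---|---|
| no change | no change | 1.00 | 1.6% |
| 0.80 | 1.00 | 1.25 | 2.0% |
| 0.60 | 0.80 | 1.33 | 2.1% |
| 0.60 | 0.90 | 1.50 | 2.4% |
| 0.50 | 1.00 | 2.00 | 3.2% |
| 0.40 | 0.80 | 2.00 | 3.2% |

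**When recording alone could double the rate.** This needs s1 = 2 × s0. As s1 cannot exceed 1, s0 must be 0.50 or less.

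**Effect on reading a real change.** If completeness moved from 0.60 to 0.80 and the recorded rate doubled, the behavioural part would be 2 / 1.33 = 1.5. That is a rise of half, not a doubling.

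**Chance of a significant result with no behavioural change** (two-sided 0.05, 634 children per site per period assumed, clustering and repeat children ignored):

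- 0.60 to 0.80: about 10% at one site, 29% with four such sites pooled.
- Any doubling of completeness: 46% at one site, 96% with four pooled.

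**The case against.** The strongest reply is that the article gives no rule saying a visit counts only if the note records a wet cough of more than four weeks. The description of chronic wet cough used here comes from PC-QoL recruitment, where the audit also picks up children with multiple presentations. A clinician-researcher may likewise infer chronicity from repeat visits when auditing health-seeking, and detailed case rules can reasonably sit in the full protocol. This stands: dependence on recorded duration is partial, not absolute. It does not remove the point, because better recording of quality and duration would still make cases easier to find.

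The size is also unknown. A reader might infer that a doubling could be wholly a charting effect. The document does not support that as a likely result: completeness pairs such as 40% to 80% give a doubling only because their ratio is 2, and electronic prompts are conditional on feasibility.

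A reader might further infer that recall and medication visits inflate the numerator. They add little to a count of parents or children, since a child already counted is not counted again. They bear mainly on the clinic-activity denominator.

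A reader might also extend the point to correct management where PBB is suspected. The article does not say that this denominator requires recorded quality and duration, so no change is asked for there.

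Finally, the recording audit already supplies much of what is needed to interpret the count, and the primary outcome is PC-QoL, not health-seeking. Both are true. But the article does not say that the two audit results will be read together.

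**Conclusion.** The concern holds in a limited form. The health-seeking count mixes parents' attendance with clinicians' recording, the program aims to change both over the same period, and the stated safeguards address neither the mixing nor its direction. If recording improves as intended, the bias is towards an apparent benefit.

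Its size cannot be fixed from the document. It could be nil if completeness does not change. It would take 1.6% to about 2.1% if completeness rose from an assumed 60% to 80%, and it could reach a full doubling only if the notes identified half or fewer of true presentations at baseline. The article's Discussion describes clinicians as often not informed about screening, which makes incomplete baseline recording plausible but gives no figure.

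The conclusion assumes that identifying a case depends at least partly on recorded cough quality and duration. It affects the first specific objective and leaves the primary PC-QoL comparison untouched.

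**What to change.** 1. Keep the audited chronic wet cough count, but describe it as recorded presentations (health-seeking plus detection). Report it beside the before-to-after change in recording of cough presence, quality and duration from the secondary-outcome audit.
2. Add a supportive health-seeking measure under one rule in both periods: children aged 0–8 with at least one parent-initiated attendance for cough, excluding clinic-initiated recall and medication visits.
3. Use individual children attending as the denominator, in place of clinic activity. This matches the eligibility criteria for parents' health-seeking and the 634 children in the sample size section, and recall and medication visits by children already counted cannot change it.
4. Attribute a rise to parents' behaviour only if the supportive measure agrees.

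The cost is an added audit definition within records already being reviewed. Each site should first check that its notes show the reason for attendance and who initiated the visit, which the article does not state. The supportive measure has two limits. Cough attendance is less specific than chronic wet cough, so the contrast is diluted. It also still depends partly on recording of cough presence, which the program targets too. It is therefore a check on the main count and does not replace it.
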